#### Exclusion criteria

No informed consentNon-atherosclerotic cause of mesenteric ischemiaAcute mesenteric ischemia (AMI)Signs of acute bowel ischemia, peritonitis, laparotomy, sepsisPrevious stent treatment in the superior mesenteric artery(ies)Target artery lesions > 4 cm in lengthUnable to cross lesion with guidewireNon-significant stenosis angiographicallyPregnancyAllergies to contrast media or stent materials

### Who will take informed consent? {26a}

Patients will be asked to provide informed consent by the project responsible physician or project nurse prior to surgery, in accordance with local and national guidelines upon providing consent, each participant will receive a copy of the informed consent document for their records.

Patients with CMI and AoCMI have variable clinical presentation but are in most cases investigated and treated within 1 week of referral. Thus, it is difficult to give a standardized inform consent timeline for the study cohort. Some will receive treatment the next morning, others the next week. Subjects are recruited from patients referred for treatment of CMI/AoCMI at the Department of Vascular Surgery, Rigshospitalet.

If, during the screening of referral data by responsible physician and/or nurse, the patient is found eligible for study inclusion, the study nurse/coordinator is contacted (scenario 1). The first contact with the patient will then be by letter or via secure email to inquire if the patient wants more information regarding the trial. If affirmative, participants receive an information letter including study information (including subjects’ rights in a health science research project) and a written consent form to be signed if the subject decides to participate in the trial. The patient is offered a further information meeting and can choose to have this by telephone or physically. The patient is allowed to have a resource person (e.g., family member, friend, or acquaintance) present during this meeting. During this meeting, the patient is informed about the project verbally as well and allowed to ask questions.

Alternatively, due to a subacute scenario (scenario 2), some AoCMI patients are approached by the clinically responsible physician and/or nurse following the first physical contact with the department to inquire if the patient wants more information regarding the trial. If affirmative, participants are handed over the information letter including study information (including subjects’ rights in a health science research project) and a written consent form to be signed if the subject decides to participate in the trial. The patient is then provided a meeting with the study nurse/physician and informed verbally as well and allowed to ask questions. The patient is allowed to have a resource person (e.g., family member, friend, or acquaintance) present during this meeting. If the patient in scenario 2, due to subacute illness, cannot provide informed consent, the patient shall be considered ineligible for the study.

The description of the research project will be given verbally in layman terms and the patient can ask questions. This meeting will take place in the outpatient clinic or department in a quiet room. The verbal information will be accompanied by a briefing of the previously provided written information describing:Risks, benefits, complications, and unpredictable risks and events to participatingAlternative treatment optionsThat patient data, including confidential and private, is protected but may be accessed by health care personnel involved in the studyThe right to withdraw at any time without supplying a reasonThat decline to participate will be universally accepted and that the patient will receive standard care

The patient will then be given a minimum of 24 h being asked again regarding participation. If the patient accepts inclusion, the informed consent is signed. In the subacute scenario (scenario 2), a minimum of 12 h will be provided before the patient is asked again regarding participation. This reduced time is to avoid unnecessary treatment delay for the patient in a subacute clinical scenario. Patients who decline participation or are not eligible for inclusion are registered in a prospective screening log.

If new information regarding effects, risks, and side effects is discovered after inclusion or during study follow-up, participants will be promptly informed. In case of study termination, participants will be informed about the cause of termination.

### Additional consent provisions for collection and use of participant data and biological specimens {26b}

The participants in the trial will provide separate consent for the storage of residual material in a biobank for future research.

## Interventions

### Explanation for the choice of comparators {6b}

The evidence for stent treatment of CMI and AoCMI is convincing, yet there are no stents that are primarily indicated for the use in the mesenteric circulation [4, 7]. Currently used stents are indicated for renal or iliac use. Furthermore, the use of covered stents (CS) for CMI has increased, partly due to recommendations from vascular societies and extrapolation from their use in other vascular beds [1, 6]. Thus, a wide variation of stents are used, and the recent literature on BMS versus CS for arteriosclerotic occlusive disease of the superior mesenteric artery are conflicting [4, 9].

### Intervention description {11a}

The procedure will take place in an angiography suite under local anesthesia. Access will primarily be gained from the femoral artery using a 6–8 Fr sheath. An alternate vascular access route, primarily the brachial artery, can be chosen at the operator’s discretion. After the target lesion has been crossed with a 0.035 guidewire, a pressure gradient across the lesion will be determined using a mean pressure gradient > 15 mmHg to define significant lesions [5]. In the case of an occlusion or near occlusion of the SMA, intra-arterial pressure measurement is omitted as it is not technically measurable. The lesion is then treated based on the pre- and intraoperative imaging. Patients with a significant lesion will then be randomized to either BMS or CS treatment. The treating physician will choose the appropriate stent length and diameter based on pre- and intraoperative imaging. The stent should cover the entire primary lesion and protrude 3–5 mm into the aorta to achieve total lesion coverage. Bare metal stent extensions (either balloon expandable or self-expandable) can be placed at the discretion of the operator to allow optimal conformity to the target vessel or minimize the risk of target vessel dissections. The stent is dilated to minimum the nominal pressure given by the manufacturer to achieve nominal stent size.

The treatment result is evaluated by standard angiography in two planes and measuring the pressure gradient across the stented segment. Two plane angiography can be substituted by on-table beam CT or angiography in one plane combined with a single X-ray in two planes to determine stent compression. Less than 30% residual stenosis and/or mean pressure gradient < 15 mmHg is considered a treatment success.

All patients will have the balloon catheter used for ballooning the stenosis/occlusion collected. Residual material from the PTA balloon and blood samples from the angioplasty catheter (< 50 ml blood) will be collected during the procedure and stored at − 80 °C in a research biobank until analysis. Peripheral blood samples (< 50 ml blood in total) will be collected in connection with PTA treatment, as well as during the yearly outpatient visits (< 50 ml) to analyze circulating blood markers.

### Follow-up

In this trial, patients will attend outpatient visits with clinical exams, blood samples, Duplex ultrasound (DUS), and quality of life (QoL) questionnaire at 6 weeks, 12 months, and then annually to 5 years postoperatively. CTA will be performed once at 12 months postoperatively, prior to the scheduled follow-up. In case of prohibitive traveling distance to the study site, the follow-up DUS at 1 year and beyond can be omitted from the protocol and replaced by CTA at investigators discretion. As the primary study endpoint is at 1 year, this alteration will not interfere with the conclusions. If there is suspicion of an in stent re-stenosis based on the clinical exam and DUS of the SMA (threshold 412 cm/s) [6], a patient will undergo a CTA. Following evaluation of CTA results and clinical examination, the patient may be offered additional treatment if indicated.

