### Strategies to improve adherence to interventions {11c}

All patients included in the COMESS trial will be followed up with clinical exam, blood samples, DUS of the visceral arteries, and QoL questionnaire at 6 weeks, 12 months, and then annually to 5 years postoperatively. During this time, information from exams, tests, and information will be gathered. CTA is performed at 12 months and will be done at the local hospital.

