## Assignment of interventions: blinding

### Who will be blinded {17a}

This is a single-blinded study. Patients and the physicians responsible for postoperative care and follow-up will be blinded to treatment allocation, until the process of unblinding.

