### Plans to promote participant retention and complete follow-up {18b}

According to the existing standard of care (SOC), follow-up after mesenteric stenting at Rigshospitalet is an outpatient visit, including clinical examination and DUS at 6 weeks and 12 months postoperatively. According to guidelines, FU after stenting of mesenteric arteries includes clinical examination and DUS at 1 month, 6 months, 12 months, and annually thereafter [9].

In this trial, annual FU outpatient visits until the fifth postoperative year, including DUS, are planned. In addition, a CTA at 12 months has been added to validate the DUS findings. In summary, because of the present study, the participating patient will receive care in better adherence to internationally accepted guidelines using of CS instead of BMS (half of the patients) and yearly FU for 5 years instead of 1 year FU only (all patients).

If a patient chooses to not participate in the trial after randomization, patients will receive care according to current SOC.

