## Statistical methods

### Statistical methods for primary and secondary outcomes {20a}

Outcomes are analyzed on intention to treat basis and secondarily per protocol. Primary outcomes will be analyzed by *t*-test and overall survival analysis, to estimate the patency at 12 months.

Secondary endpoints will be analyzed by survival analysis techniques, such as Kaplan–Meier curve and log-rank tests. ANOVA repeated measures will be used to estimate comparison QoL between the two groups, and secondary stent patency. Log-rank test will be used to compare the survival rates between groups. Sensitivity and specificity of CTA and US will be analyzed with a logistic regression and receiver operator curves (ROC) analysis.

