#### Radiation risk

CTA at 12 months has been added to validate the DUS findings. The additional radiation exposure to the patient is negligible, with approximately 2–8.6 mSv over the 5-year study period. The natural background exposure in Denmark is around 3 mSv annually [11]. The added radiation exposure of 2–8.6 mSv will increase the cancer risk in the individual patient with 0.08% providing a total lifetime cancer risk to 25.08% from 25%.

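### The 12-month CTA added to validate duplex ultrasound is scheduled before the ultrasound, and no masking of the ultrasound to the CTA is stated, so ultrasound accuracy may be overstated

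*Protocol article*

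**What the plan says.** The Follow-up section of the protocol article fixes both tests at 12 months. For the visit: "patients will attend outpatient visits with clinical exams, blood samples, Duplex ultrasound (DUS), and quality of life (QoL) questionnaire at 6 weeks, 12 months". For the CTA: "CTA will be performed once at 12 months postoperatively, prior to the scheduled follow-up". Strategies to improve adherence {11c} adds: "CTA is performed at 12 months and will be done at the local hospital".

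The purpose of the scan is given twice. In Plans to promote participant retention {18b}: "a CTA at 12 months has been added to validate the DUS findings". In Radiation risk, where the added exposure is justified: "CTA at 12 months has been added to validate the DUS findings". The accuracy of CTA and ultrasound is listed among the secondary endpoints, and Statistical methods {20a} says: "Sensitivity and specificity of CTA and US will be analyzed with a logistic regression and receiver operator curves (ROC) analysis".

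On masking, Who will be blinded {17a} says only this: "Patients and the physicians responsible for postoperative care and follow-up will be blinded to treatment allocation, until the process of unblinding". The article does not say whether the person doing the DUS is kept from the CTA result. Follow-up also gives a velocity threshold of 412 cm/s, used with the clinical examination to raise suspicion of in-stent restenosis, and it lets the DUS at 1 year and later be replaced by CTA for patients who live far away.

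**The concern.** In a validation, the test under evaluation should be done and recorded without knowledge of the reference result. Here the scheduled order puts the reference first, and the only stated blinding concerns a different piece of information, the stent type. An operator who knows that a restenosis is present, or has been excluded, may sample more or less thoroughly, or settle a borderline finding to agree with the CTA. If that happens, agreement rises and both sensitivity and specificity move upwards.

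The 12-month pair carries most of the information for this endpoint. Surveillance is a named objective of the trial, and an inflated accuracy estimate would make DUS alone look more dependable for follow-up than it is.

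**Working it through.** **1. The statements side by side.** The CTA comes before the visit (Follow-up). The DUS is done at the visit (Follow-up; {11c}; Table 1). The CTA is there to validate the DUS ({18b}; Radiation risk). Accuracy is an endpoint (Secondary endpoints; {20a}). Blinding is to allocation ({17a}). So the reference test precedes the test it validates, and no stated rule separates them.

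**2. Why 12 months matters.** At baseline, inclusion requires more than 50% stenosis of the superior mesenteric artery on CTA, so all randomised patients are CTA-positive for that vessel and their data cannot give a specificity. At the other follow-up visits, a paired CTA is prompted by suspicion from the clinical examination and DUS, so DUS-negative patients are mostly unverified. Twelve months is the only scheduled follow-up point at which both tests are done whatever the result, apart from patients whose DUS is omitted for distance.

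**3. The plan's own figure.** The article gives no figure for the accuracy endpoint. Its sample size for the primary endpoint does reproduce. Reading the planning rates of 85% and 60% as freedom from restenosis, with two-sided alpha 0.05 and power 0.80, the mean rate is 0.725 and

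n = [1.960 × √(2 × 0.725 × 0.275) + 0.842 × √(0.85 × 0.15 + 0.60 × 0.40)]² / 0.25² = 48.9, so 49 per arm and 98 in total (power 0.801 at 49 per arm).

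This does not bear on the point, except that it gives an expected number of restenoses: 49 × 0.15 + 49 × 0.40 = 26.95, about 27 with and 71 without.

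**4. Possible size of the bias.** Let r be the share of wrong DUS readings that change to agree with a known CTA. Then apparent accuracy = true + r × (1 − true). The true values and r are assumptions; none is in the documents.

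| True sensitivity / specificity | r = 0 | r = 0.10 | r = 0.25 | r = 0.50 |
|---|---|---|---|---|
| 0.70 / 0.80 | 0.70 / 0.80 | 0.73 / 0.82 | 0.775 / 0.85 | 0.85 / 0.90 |
| 0.80 / 0.85 | 0.80 / 0.85 | 0.82 / 0.865 | 0.85 / 0.887 | 0.90 / 0.925 |
| 0.90 / 0.95 | 0.90 / 0.95 | 0.91 / 0.955 | 0.925 / 0.962 | 0.95 / 0.975 |

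For r from 0.10 to 0.50, sensitivity is too high by 1 to 15 points and specificity by 0.5 to 10 points. At r = 0 there is no bias.

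**5. Set against precision.** If all 98 patients gave a pair, the 95% half-width at a true value of 0.80 would be 1.96 × √(0.80 × 0.20 / 27) = 0.15 for sensitivity and 1.96 × √(0.80 × 0.20 / 71) = 0.09 for specificity. Omitted DUS and losses to follow-up would widen both.

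**The case against.** The strongest reply is that order is not access. The article fixes when the CTA is acquired, not who sees the result and when, and the scan is done at the local hospital, away from the study-site DUS. A reader might infer that the DUS is done with the CTA result in hand and that accuracy will be overstated. The documents do not support that: nothing says the operator sees the CTA. Nor does anything say that the operator does not, and a different location is not masking.

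Second, reading rules for a secondary endpoint may sit in the full protocol or analysis plan, which are not shown. This would settle the matter if the article were merely silent. But it states a sequence that works against the purpose it states for the scan. If a masking rule exists, it only needs to be cited.

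Third, having the CTA first protects the CTA reading from the same-visit DUS, and DUS first would carry the mirror-image risk. This stands, and it is why the dates need not change.

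Fourth, a measured velocity against 412 cm/s leaves less room for expectation than a subjective grade. This also stands in part. The recorded velocity still depends on where and how carefully the operator samples, an ROC analysis of those velocities would inherit that, and suspicion also rests on the clinical examination.

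Fifth, any figure for the bias is assumed, not all 98 patients need have a pair, and random error in sensitivity is about as large as the biggest bias shown. All true. However, bias does not shrink with more patients and the confidence interval does not show it.

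**Conclusion.** The point holds as a risk. The stated order lets the CTA result be known when the 12-month DUS is acquired and classified, no masking of one to the other is stated, and DUS sensitivity and specificity at 12 months may therefore be overstated. If the CTA is known, the direction is upward. The size cannot be derived from the documents: it is zero without access, and the table shows only what assumed rates would give.

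The scope is one part of one secondary endpoint. A reader might infer that the primary patency comparison is affected too. That would require patency to be judged by DUS, which the article does not state. The sample size is unaffected.

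**What to change.** Keep the 12-month dates and add to the Follow-up section that the person performing the 12-month DUS has no access to the CTA result, and that the DUS velocity and classification are entered in REDCap with a timestamp before the CTA result is disclosed to that person. Clinical reporting and handling of the CTA stay as they are.

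For the analysis, use all available DUS/CTA pairs. Flag those in which the order was broken or a reintervention fell between the two tests, and report the accuracy with and without them as a sensitivity analysis. Dropping them from the main estimate would tend to remove clear restenoses from an already small positive group, and so introduce a selection bias. Enrolment began in June 2023, so some 12-month visits may already have taken place; pairs for which the order cannot be shown should be flagged in the same way.

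The cost is a short addition to the visit procedure and one timestamped field, with no extra reader, visit or test. The downside is small: some pairs will be unmasked when a CTA finding must be acted on before the DUS.

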### Secondary endpoint(s)—evaluated at 12 months and 5 years

Secondary stent patencyFreedom from stent re-stenosis (luminal diameter > 50%)Freedom from reinterventionOverall survivalIntervention free survivalFreedom from symptom recurrenceProteomics assay signal (balloon) and concentration of established biomarkers (blood samples)Quality of lifeSensitivity and specificity of CTA and US preoperatively and during follow-up

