### Participant timeline {13}

See Tables 1 and 2.

**Table 1 Tab1:** Standard participant timeline

Enrolment	Baseline	6-week follow-up	12-month follow-up	2-year follow-up	3-year follow-up	4-year follow-up	5-year follow-up
Informed consent	X						
EQ-5D-5L	X	X	X	X	X	X	X
SF-36	X	X	X	X	X	X	X
Medical history	X						
Physical examination	X	X	X	X	X	X	X
CT-angiography	X		X				
Duplex ultrasound	X	X	X	X	X	X	X

**Table 2 Tab2:** Modified participant timeline

Enrolment	Baseline	6-week follow-up	12-month follow-up	2-year follow-up	3-year follow-up	4-year follow-up	5-year follow-up
Informed consent	X						
EQ-5D-5L	X	X	X	X	X	X	X
SF-36	X	X	X	X	X	X	X
Medical history	X						
Physical examination	X	X					
CT-angiography	X		X				
Duplex ultrasound	X	X					
Telephone consultation		X	X	X	X	X	X

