### Sample size {14}

In the only study investigating CS vs BMS in CMI [10], a retrospective non-randomized study of 225 patients, patients treated by CS had freedom from restenosis of 92% ± 6% compared to BMS with freedom restenosis of 53% ± 4% [10]. This study suffered several limitations that must be considered for a sample size estimation in the present RCT: the velocity cut-off used may overestimate high-grade restenosis, the follow-up was significantly longer in the BMS group, and differences in time-dependent outcomes including restenosis must be expected. In addition, a general underreporting of outcomes in both the BMS and the CS arm must be expected in a retrospective study. Therefore, the expected restenosis rates were adjusted to 85% and 60%.

Using dichotomous endpoints (restenosis: Y/N), a two independent sample study, alpha = 0.05, beta = 0.2, and power = 0.8, sample size was estimated to 49 patients in each group (total = 98). With 120 CMI/AoCMI patients treated yearly in Copenhagen, an estimated inclusion rate of 80% and 20% dropout, a total of 77 CMI patients will be randomized yearly (app 6 pts/month)—and 98 patients are expected included within 18–24 months.

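### Ultrasound accuracy outside the 12-month visit, including the 5-year evaluation, carries partial-verification bias, and follow-up CTA has no scheduled independent reference

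*Protocol article*

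**What the plan says.** All of this is in the protocol article.

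- **Endpoint.** The last of the nine secondary endpoints is the sensitivity and specificity of both CTA and ultrasound, before treatment and in follow-up. The header over the list reads "evaluated at 12 months and 5 years".
- **CTA schedule.** The Follow-up section states: "CTA will be performed once at 12 months postoperatively, prior to the scheduled follow-up". The CTA row of Table 1 (Participant timeline {13}), "CT-angiography X X", marks baseline and 12 months only. DUS is marked at baseline, 6 weeks, 12 months and every year to year 5.
- **Other routes to CTA.** A patient has a CTA under this condition: "If there is suspicion of an in stent re-stenosis based on the clinical exam and DUS of the SMA (threshold 412 cm/s". Where travel is prohibitive, "the follow-up DUS at 1 year and beyond can be omitted from the protocol and replaced by CTA at investigators discretion". Table 2, the modified timeline, shows no DUS after 6 weeks and a follow-up CTA at 12 months only.
- **Role of CTA.** Radiation risk says "CTA at 12 months has been added to validate the DUS findings", and section {18b} says the same.
- **Analysis.** Section {20a}: "Sensitivity and specificity of CTA and US will be analyzed with a logistic regression and receiver operator curves (ROC) analysis". It does not say which visits or which CTAs enter.

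**The concern.** To estimate sensitivity and specificity, the reference test must be done regardless of the index test result, or the dependence must be corrected for. Outside 12 months the CTA that would serve as reference for DUS is ordered largely because DUS was abnormal. Patients with normal DUS are then seldom verified, so false negatives and true negatives go mostly unobserved. Sensitivity is pushed up and specificity down. An ROC curve from such pairs would also lack most velocities below 412 cm/s.

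CTA has a separate problem. If it validates DUS in follow-up, its own follow-up accuracy needs another standard, and none is scheduled. Any angiography at that stage would come from patients already selected on CTA for possible re-treatment.

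The Objectives include the value of intensified surveillance, which rests on annual DUS. A sensitivity close to 100% that the design itself produces could be read as support for that surveillance.

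**Working it through.** **The plan's own figure.** The article gives no number for the accuracy endpoint. Its only related figure is the sample size, based on "the expected restenosis rates were adjusted to 85% and 60" percent. These read as freedom from restenosis, so they imply restenosis of 15% and 40%. With a two-sided alpha of 0.05 (sidedness is not stated), 80% power and mean proportion 0.725:

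n = [1.96·√(2·0.725·0.275) + 0.8416·√(0.85·0.15 + 0.60·0.40)]² / 0.25² = (1.238 + 0.510)² / 0.0625 ≈ 48.9, so 49 per arm.

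This matches the article and is not in dispute.

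**Assumptions that are not in the document.** True DUS sensitivity (Se) is 0.80 and specificity (Sp) 0.90. All DUS-positive patients get CTA, and a share v of DUS-negative patients do. CTA is taken as the truth.

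**One visit with triggered CTA.**

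Apparent Se = 0.8 / (0.8 + 0.2v)

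Apparent Sp = 0.9v / (0.9v + 0.1)

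| v | apparent Se | apparent Sp |
|---|---|---|
| 0 | 1.00 | 0.00 |
| 0.05 | 0.99 | 0.31 |
| 0.10 | 0.98 | 0.47 |
| 0.20 | 0.95 | 0.64 |
| 0.50 | 0.89 | 0.82 |
| 1 | 0.80 | 0.90 |

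Prevalence cancels. The row v = 0 holds whatever the true values are. The row v = 1 is the 12-month visit on the standard timeline, where the bias is zero. At v = 0.10 a true 0.90/0.95 appears as 0.99/0.66, and a true 0.90/0.80 as 0.99/0.29.

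**Pooling with the 12-month pairs.** Take v = 0 outside 12 months, with equal numbers and equal prevalence at each visit.

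- 12 months plus year 5: Se = (0.8 + 0.8)/(1.6 + 0.2) = 1.6/1.8 = 0.89. Sp = 0.9/(0.9 + 0.1 + 0.1) = 0.9/1.1 = 0.82.
- All six visits (6 weeks, 12 months, years 2 to 5): Se = 4.8/(4.8 + 0.2) = 0.96. Sp = 0.9/(0.9 + 0.6) = 0.60.

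The loss of specificity is about 8 points in the first case and 30 in the second. Sensitivity is overstated by about 9 and 16 points.

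**Precision of the 12-month data alone.** If all 98 patients are paired and prevalence is 27.5% (the mean of 15% and 40%), about 27 have restenosis and 71 do not. The 95% half-widths are:

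- Se: 1.96·√(0.8·0.2/26.95) = 0.15
- Sp: 1.96·√(0.9·0.1/71.05) = 0.07

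Dropout and modified-timeline patients would widen both.

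**The case against.** The strongest reply is that the main comparison is already sound. Every standard-timeline patient has CTA and DUS at 12 months whatever DUS shows, and the article says that CTA is there to validate DUS. That stands. A reader might infer that the whole follow-up accuracy endpoint is biased, but the schedule does not support this for 12 months.

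Four further points narrow the concern:

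- **Pooling is not stated.** Section {20a} names methods, not which pairs enter, and an SAP could settle that. The pooled figures above show what would happen, not what is announced. An SAP could not rescue a 5-year estimate, however: a correction for verification bias needs some verified DUS-negative patients, and the imaging schedule provides none by design.
- **The 5-year header covers nine mixed endpoints.** It fits some poorly, including the preoperative half of this one. It is still the only stated evaluation time, and this endpoint explicitly extends into follow-up.
- **Late CTA is not reserved for positive DUS.** The travel provision is another route, and clinical suspicion may prompt some CTAs. Patients whose DUS is replaced by CTA have no paired DUS, so they do not reduce the bias.
- **CTA does have a comparator before treatment,** namely angiography or pressure gradient. It would be wrong to read the article as giving CTA no reference at all; the gap is in follow-up.

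Nor does the article say that the trial will re-derive the 412 cm/s threshold. It uses that value as a trigger and cites a source for it.

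**Conclusion.** The point holds for DUS accuracy outside the 12-month visit, including the 5-year evaluation, and for the accuracy of CTA in follow-up. With no DUS-negative patient verified, estimates from those visits alone are fixed at 100% sensitivity and 0% specificity. Under the assumed true 80%/90%, pooling with 12-month data gives between about 89%/82% (one added visit) and 96%/60% (all six visits). These sizes depend on the assumed accuracy, on full verification of DUS-positive patients and on equal visits; the direction does not, as long as DUS-positive patients are verified more often than DUS-negative ones.

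From the single-visit table one might claim a specificity bias of 26 to 90 points (v from 0.20 down to 0). That range describes triggered pairs taken alone. It is not the error of an analysis that also contains the 12-month pairs.

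This is a secondary endpoint. Randomization, the primary comparison and the sample size are untouched. A change is worth making because the article commits to an evaluation that its own imaging schedule cannot support.

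**What to change.** Change the wording of the secondary endpoint list and section {20a}:

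1. Estimate DUS sensitivity, specificity and ROC only from the scheduled 12-month visit, in patients with both tests. Name the protocol CTA as reference.
2. Require the 12-month DUS to be read and recorded without sight of the CTA, because the CTA is done before that visit. This needs one case report form instruction.
3. State that modified-timeline patients (Table 2) have no 12-month DUS and are not in this analysis.
4. Keep DUS-triggered CTA pairs out of sensitivity, specificity and ROC. Report them descriptively as the positive predictive value of the trigger.
5. Remove the 5-year evaluation of this endpoint and the follow-up sensitivity and specificity of CTA.

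The cost is fewer pairs, with precision of about ±15 points for sensitivity and ±7 for specificity at best, on the assumptions above. No extra imaging and no change to patient care are needed.
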